#### Baseline measurements

All GP practices recruited will be asked to complete a baseline questionnaire prior to randomisation to allow capture of practice characteristics. This includes: (i1) practice staff composition (GP partners/salaried/sessional nurse practitioners and practice nurses and locums used in the last 12 months); (2) available characteristics (such as postcode, total patients registered); (3) registered child patients—number, age group, ethnicity and gender; (4) triage systems used to handle children presenting with acute cough and RTI and (5) which clinicians prescribe antibiotics to children aged 0–9 years.

#### Randomisation

GP practices will be randomised on a 1:1 basis by the independent BRTC. Randomisation of practices will be stratified by CCG, with further minimisation by practice list size and baseline dispensing rates of 0–9 year olds; calculated using data from the 12 months prior to the CCG joining the CHICO study. A trial schematic is shown in figure 1.

**Figure 1 F1:**
[figure not shown]
Trial schematic. CCGs, Clinical Commissioning Groups.

#### Follow-up measurements

A follow-up questionnaire will be sent to all practices after 12 months (similar to the baseline questionnaire) asking about staffing levels and management of RTI among children as well as use of intervention for those in the intervention arm. Questions will also be included about whether the practice has merged or split with another practice, if they have had any related fatalities in children aged 0–9 years during the 12 months participation and for intervention practices only, their experience of using the intervention, problems encountered and whether they would use it again.

### Blinding

As this is a cluster RCT and due to the nature of the intervention delivery, it will not be possible to blind the practices to their allocation of either control or intervention group. Administrative staff will have access to individual data items, for entry into the database. The statistician will have access to aggregate information, by arm, to be able to report to the DMC and monitor hospitalisations.

### Outcomes

The primary and secondary outcomes are listed in table 2. All practices will collect data over a 12-month period, thus any seasonal fluctuations will be captured.

**Table 2 T2:** Detailed study outcomes

**Primary outcomes**	
P1)	Whether the CHICO intervention decrease the number of dispensed prescriptions for oral amoxicillin and macrolide antibiotics* (efficacy comparison).
P2)	Whether the CHICO intervention result in no increase in hospital admissions† for children with a hospital diagnosis of RTI (non-inferiority comparison).

### Safety reporting

Adverse events (AE) and serious AEs (SAE) will be recorded and reported in accordance with Good Clinical Practice guidelines and the Sponsor’s Research Related Adverse Event Reporting Policy. This trial is a low risk study, SAEs will only be reported if they are fatal or serious and potentially related to trial participation (ie, they result from advice provided by the intervention algorithm). As one of the outcomes for the trial is hospitalisation, we do expect some participants to be admitted to hospital (due to a deterioration of their underlying illness). Hospitalisation due to RTI is an expected SAE and will not be subject to expedited reporting. Both SAEs and hospitalisation rates will be regularly reported to the DMC who will raise any safety concerns to the trial team and TSC for further action. Expected SAEs include but are not limited to pneumonia, empyema, deteriorating bronchiolitis.

#### SAEs related to the use of intervention

If the GP practice champion or attending clinician suspects that an SAE resulted from use of the intervention it should be reported to the study team immediately. The causality of the event will be assessed by the practice clinician and a delegated clinician working within the CHICO study team. If the event is deemed to be probably or definitely related to the intervention the SAE will be reported to the Research Ethics Committee and sponsor according to the expedited timescales.

#### Fatal SAEs

All practices should inform the study team immediately of any fatal SAEs in children that had presented with RTI at a practice consultation and were 0–9 years old at the time of consultation. This applies to any deaths occurring within 90 days of the consultation.

### Internal pilot study

An internal pilot phase lasting 3 months and using 4 or more CCGs to recruit 60 practices will help establish how many CCGs we will eventually need to approach. Stop-go (traffic light) criteria will be used for (1) practice recruitment, (2) identification of a practice champion, (3) intervention use and (4) ability to obtain dispensing data from the CCGs. A green light will be given for 80+% success (90% for dispensing data) and an amber light to implement remedial action at 70%–79% (80%–89% for dispensing data). A red light would indicate either a further pilot is needed or stopping the trial.

### Sample size determination

Both sample size calculations assume 90% power and a conservative two-sided alpha of 0.025 to take account of the two coprimary outcomes. Both sample sizes also assume an intracluster correlation coefficient of 0.03 (which has been described as the upper CI for ICCs in efficient cluster randomised trials,^14 15^ an estimated coefficient of variation of 0.65 (to take account of differences in cluster size^16^ and an assumption of 750 children on average aged 0–9 years registered per practice (based on Bristol & Bath CCG data). Expected differences assumed: (1) a reduction in dispensing rate from 33 prescriptions per 100 registered children aged 0–9 years to 29 (or fewer) prescriptions (ie, ≥10% overall reduction); and (2) a hospitalisation rate that is no more than 2% in the intervention arm, compared with the control arm which is estimated to be 1%. This is based on a non-inferiority margin of 1%, however, the investigators wanted to err on the side of caution and use a two-sided alpha for the sample size calculation. This gave an overall sample size requirement of 310 practices; 155 intervention and 155 control practices.

### Economic evaluation

To address our secondary aims (S2) a focus on costs will clarify whether and by how much NHS costs might change in the event of a widespread deployment of the algorithm into routine clinical practice. Given the light-touch efficient design of the trial, the economic evaluation will be limited to a between-arm comparison of mean NHS costs in a cost–consequence analysis. NHS costs will be calculated from the costs of the intervention itself, prescriptions of amoxicillin and macrolides per the coprimary outcome, ED attendances and hospital admissions.

### Qualitative study

Qualitative interviews with clinicians (GPs and practice nurses) and other practice staff (managers, pharmacists) and CCG staff (medicines managers) will explore the use of the intervention, how it was embedded into practice and whether it was used appropriately. The interview topic guide will be informed by normalisation process theory (NPT) developed to explain the social processes leading to routine embedding of complex interventions in healthcare.^17 18^

NPT proposes that implementation of interventions is dependent on the ability of participants to fulfil four criteria; ‘coherence’ (how people make sense of the intervention), ‘cognitive participation’ (the work to develop new practices), ‘collective action’ (the work to operationalise practices) and ‘reflexive monitoring’ (ways in which people appraise how new practices are working).

Clinicians and other key staff from the intervention practices will be invited to participate in semistructured interviews to explore their views and experiences of the intervention. Audio recorded verbal consent will be taken from participants. The first set of interviews will be conducted during the internal pilot phase and findings fed back to help guide best practice during the rest of the study. A second phase of interviews will be conducted when the clinicians have been using the intervention for several months to investigate the normalisation and sustainability of using the intervention. Interviews are expected to take 30–45 min.

Purposive sampling will be used to include a maximum variation sample to take account of: clinical experience, dispensing rates of practices and practices serving areas of high and low socialeconomic deprivation. The sample sizes will be determined by the need to achieve data saturation, such that no new themes are emerging from the data by the end of data collection.^19^ Interviews will be analysed in batches. This is likely to include up to 30 clinicians and 20 other staff involved in implementation.

### Data analysis

#### Quantitative data analysis

All analyses and reporting will be in line with Consolidated Standards of Reporting Trials (CONSORT) guidelines and its extension for cluster randomised trials.^20^ Primary analyses will be conducted on an intention-to-treat basis, a per-protocol analysis will also be conducted as part of the sensitivity analyses. A full CHICO statistical analysis plan will be developed and agreed by the TSC prior to undertaking analyses of the main trial. The statistical analysis plan will include health economics and qualitative analysis subsections. At the end of the trial, all outcomes will be described and compared with the appropriate descriptive statistics where relevant: mean and SD for continuous and count outcomes, medians and IQR if required for skewed data and numbers and percentages for dichotomous and categorical outcomes. Depending on the dispersion of the data we may use linear regression or a random effects Poisson regression (negative binomial regression) model to analyse both coprimaries, with CCG included as a random effect. This has the advantage of incorporating person-years follow-up (number of children at a practice multiplied by the length of follow-up for that practice) and examining clustering by CCG. Each coprimary will be adjusted for baseline dispensing rates or hospitalisation rates, using the 12 months of data collected prior to randomisation. Effects of number of practices within CCGs and number of patients within each practice will also be investigated in a sensitivity analysis. Other baseline characteristics between practices will be examined to ensure randomisation is balanced in the two arms. Any differences in excess of 0.5 SDs or 10% or more will be controlled for in sensitivity analyses to ensure that the imbalance does not affect the overall result. The effects of missing data will be explored using sensitivity analyses. We anticipate no more than 10% missing data and that it will be missing at random. The pattern and extent of missing data will be explored and any changes to the methods described in the analysis plan will be fully justified in the study report and publication. All quantitative data will be analysed using Stata version 15.

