**Methods and analysis:**

The coprimary outcomes are (1) practice rate of dispensed amoxicillin and macrolide antibiotics, (2) hospital admission rate for RTI using routinely collected data by Clinical Commissioning Groups (CCGs). Data will be collected for children aged 0–9 years registered at 310 practices (155 intervention, 155 usual care) over a 12-month period. Recruitment and randomisation of practices (using the Egton Medical Information Systems web data management system) is conducted via each CCG stratified for children registered and baseline dispensing rates of each practice. Secondary outcomes will explore intervention effect modifiers. Qualitative interviews will explore intervention usage. The economic evaluation will be limited to a between-arm comparison in a cost–consequence analysis.

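### List size is a covariate in neither primary model, and baseline dispensing is not in the admissions model, although allocation is minimised on both; adding them is a free improvement

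*Protocol article*

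**What the plan says.** The Randomisation section of the protocol article sets out the allocation: "Randomisation of practices will be stratified by CCG, with further minimisation by practice list size and baseline dispensing rates of 0–9 year olds". The baseline figures for this are "calculated using data from the 12 months prior to the CCG joining the CHICO study". The abstract names the same two practice-level factors: "stratified for children registered and baseline dispensing rates of each practice".

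The Quantitative data analysis section leaves the choice between linear and count regression open, and describes the "model to analyse both coprimaries, with CCG included as a random effect". On covariates it says: "Each coprimary will be adjusted for baseline dispensing rates or hospitalisation rates, using the 12 months of data collected prior to randomisation". The count model is favoured partly for "incorporating person-years follow-up (number of children at a practice multiplied by the length of follow-up for that practice". List size appears again only here: "Effects of number of practices within CCGs and number of patients within each practice will also be investigated in a sensitivity analysis".

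The footnotes to Table 2 make the number of registered children aged 0–9 (median monthly list size) the denominator of both rates.

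**The concern.** When allocation is forced to balance a prognostic factor, the treatment estimate varies less from trial to trial than under simple randomisation. A model that omits the factor does not recognise this. Its standard error then describes a less well-balanced design than the one used, so intervals are wider than they need be and tests reject slightly too rarely. Including the factor corrects the calibration and also removes the variance that the factor explains.

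The article is not silent here. It names the primary covariates and places practice size in a sensitivity analysis, so an analysis plan that follows the article would carry the omission forward. The admissions model is the more exposed: it contains neither minimisation factor as a covariate. An unnecessarily large standard error there makes non-inferiority harder to show.

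Using list size as a denominator or person-years exposure does not substitute for adjustment. It scales expected events in proportion to list size, but does not let the rate itself differ between small and large practices.

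**Working it through.** **1. Randomisation factors against primary models**

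| Factor | Role in allocation | Dispensing model | Admissions model |
|---|---|---|---|
| CCG | Stratification | Random effect | Random effect |
| Baseline dispensing rate | Minimisation | Covariate | Absent |
| List size | Minimisation | Denominator/exposure; sensitivity only | Denominator/exposure; sensitivity only |
| Baseline admission rate | None | Absent | Covariate |

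**2. The plan's own sample size**

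Inputs from Sample size determination: 90% power, two-sided alpha 0.025, ICC 0.03, coefficient of variation 0.65, 750 children per practice, 33 v 29 per 100 for dispensing, 1% v 2% for admissions, 310 practices.

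- Design effect = 1 + ((1 + 0.65²) × 750 − 1) × 0.03 = 32.98.
- Dispensing: 3317 per arm by the pooled two-proportion formula; 3317 × 32.98 / 750 = 145.9, so 146 practices per arm and 292 in total.
- Admissions: 3666 per arm; 3666 × 32.98 / 750 = 161.2, so 162 per arm and 324 in total. The arcsine formula gives 314.
- At 155 per arm, the effective n is 155 × 750 / 32.98 = 3525 per arm, giving power of 91.8% for dispensing and 88.8% for admissions.

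No single formula returns exactly 310 for both outcomes, but power at 310 is within 2 points of 90% for each. No term in the stated calculation represents covariate adjustment.

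**3. Size of the possible gain**

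Let R² be the share of remaining outcome variance that the omitted factors explain after the outcome's own baseline. The documents give no value, so this range is assumed. SE ratio = √(1 − R²); effective n = 3525 / (1 − R²).

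| R² | SE ratio | Power, dispensing | Power, admissions |
|---|---|---|---|
| 0 | 1.000 | 91.8% | 88.8% |
| 1% | 0.995 | 92.1% | 89.1% |
| 2% | 0.990 | 92.3% | 89.4% |
| 5% | 0.975 | 93.1% | 90.4% |
| 10% | 0.949 | 94.4% | 91.9% |

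**4. Calibration, by simulation**

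Assumptions: 310 practices in 31 CCGs of 10; biased-coin minimisation within CCG on tertiles of list size and baseline dispensing; linear model without a CCG term; 4000 runs per scenario; nominal size 0.025. The implied R² is 1 − (fully adjusted model SE / own-baseline model SE)².

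| Coefficients (list size, dispensing) | Own baseline only: model SE / empirical SE / size | All factors: model SE / empirical SE / size | Implied R² |
|---|---|---|---|
| 0, 0 | 0.0911 / 0.0905 / 0.0227 | 0.0912 / 0.0907 / 0.0230 | 0 |
| 0.1, 0.1 | 0.0910 / 0.0911 / 0.0270 | 0.0898 / 0.0903 / 0.0270 | 2.6% |
| 0.2, 0.1 | 0.0909 / 0.0890 / 0.0210 | 0.0874 / 0.0864 / 0.0262 | 7.6% |
| 0.3, 0.2 | 0.0907 / 0.0865 / 0.0200 | 0.0814 / 0.0815 / 0.0255 | 19.5% |

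The Monte Carlo standard error of a size near 0.025 is √(0.025 × 0.975 / 4000) = 0.0025, so small differences in size should not be over-read. With no residual prognostic effect, adjustment costs nothing visible. With weak effects the model SE changes by about 1%. Only in the strongest scenario is the unadjusted model SE clearly too large, by 0.0907 / 0.0865 − 1 = about 5%.

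**The case against.** The strongest reply is that the plan already holds most of what matters. CCG is in both models, baseline dispensing is in the dispensing model, and the admissions model carries its own 12-month baseline, plausibly its best practice-level predictor. List size already sets the denominator, so what remains is any association between size and rate after baseline adjustment, and nothing in the document says that this is material. The article also defers to a full analysis plan, leaves the model family open, and promises sensitivity analyses for imbalanced baseline characteristics. All of this limits the size of the point. It does not remove it, because the article assigns list size to a sensitivity analysis explicitly.

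Three stronger readings are tempting, and the documents do not support them.

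- *Standard errors are wrong and precision is lost.* This holds only if the omitted factors predict the outcome beyond its own baseline, which the documents do not establish.
- *The true test size falls well below nominal.* If balance were perfect, size would be 2(1 − Φ(2.2414/√(1 − R²))): 2.1%, 1.8% and 1.2% for R² of 5%, 10% and 20%. Minimisation does not balance perfectly. At an implied R² of about 19.5%, the simulation gave 2.0%, so those figures are an extreme case and not an estimate for this trial.
- *The omission leaves the trial underpowered.* The sample size takes no stated credit for adjustment, so the loss is forgone gain. The 88.8% for admissions comes from the choice of formula, not from the covariates.

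**Conclusion.** The mismatch between allocation and primary models is real on the natural reading of the text, but it is narrow: list size in both models, baseline dispensing in the admissions model. Any consequence is conditional and conservative. Over the assumed residual R² of 0 to 10%, adjustment would reduce the standard error by about 0 to 5%, and raise power by about 0 to 3 points for admissions and 0 to 2.6 points for dispensing. There is no risk of a false claim of efficacy or of non-inferiority from this source. The calibration results rest on assumed minimisation categories and a linear model without CCG. This is a free improvement, not an error that invalidates the analysis.

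**What to change.** Specify list size as a covariate in both primary models and baseline dispensing rate as a covariate in the admissions model, alongside CCG and the outcome's own baseline rate. Keep the person-years exposure if a count model is used. Make the models without the added factors the sensitivity analysis, reversing the present order for list size. State which baseline window supplies the dispensing covariate, since allocation uses the year before the CCG joined and the analysis uses the year before randomisation.

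The cost is wording in the analysis plan. Both variables are needed to randomise, so they should be held for every practice. If each enters as one linear term, the dispensing model spends one more degree of freedom and the admissions model two, out of 310 practices. The sample size does not change.

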#### Qualitative data analysis

Interviews will be transcribed and anonymised. Analysis will inform further data collection, for instance, analytical insights from data gathered in earlier interviews will help identify any changes that need to be made to the topic guides during later interviews. Qualitative analysis of the transcripts will follow recognised thematic analysis procedures using NVivo software.^21^ Thematic analysis,^22^ using a data-driven inductive approach,^23^ will be used to scrutinise the data in order to identify and analyse patterns and themes of particular salience for participants and across the dataset.^24^

### Study duration and timeline

The initial duration was 33 months from 1 March 2018 to 30 November 2020 although a subsequent extension of 12 months has been awarded to extend the study to 30 November 2021 to recruit the target number of practices. The timeline includes study set up (8 months), internal pilot (3 months), recruitment of practices via CCGs (15 months), follow-up of data collection (12 months) and analysis (7 months).

### Study management

The study will be monitored and audited in accordance with the Sponsor’s policy, which is consistent with the UK Policy Framework for Health and Social Care Research. The following data monitor checks will be carried out by the coordination team; that data collected are consistent with adherence to the study protocol; that Case Report Forms (CRFs) are only being completed by authorised persons; that SAE recording and reporting procedures are being followed correctly and that no key data are missing and that data are valid.

### Trial oversight

The study is overseen by a trial management group that meet on a monthly basis and consist of the chief investigator (CI), grant holders, study sponsor and any other staff responsible for the delivery of the trial. The TSC provide independent supervision of the trial and oversees trial progress. The TSC consists of an independent chair (GP and Clinical Academic) and four other independent members including a statistician, a second clinician and two patient and public involvement representative, as well as the CI. The DMC monitors patient safety and trial data efficacy and consists of an independent chair, two other independent members, the CI and trial statistician.

All SAE’s are recorded and notified as appropriate to the relevant authorities. The University of Bristol is acting as sponsor for this trial and is responsible for overall oversight of the trial.

## Ethics and dissemination

### Ethics

We are not recruiting individual patients to this study and the primary outcome data are already collected routinely, thus, we do not need patient consent. We will consent the individual practices and encourage all clinicians in the intervention practices to use the intervention tool appropriately. The intervention is directed at the clinician primarily to change their prescribing behaviour. Any data collected from individual clinicians will be anonymised. The personalised letter given to the patients will not contain information on risk of hospitalisation, but rather details of the consultation and the usual safe-guarding information. The CHICO RCT falls under the remit of draft guidance^25^ for ‘simple and efficient trials’ due to the nature of the intervention and the low level of risk involved for patients and meets the suggested principles provided by NHS Health Research Authority.^26^

